We will select a subset of apixaban patients from our EHR pool to create a cohort that matches the ARISTOTLE apixaban participants on a selection of the following baseline characteristics:

Age.Sex.Body mass index (BMI).Systolic blood pressure (SBP).Congestive heart failure or left ventricular systolic dysfunction.Hypertension requiring treatment.Diabetes mellitus.Prior stroke/thromboembolism.Smoking status.Alcohol consumption.Level of renal impairment.Prior VKA/warfarin exposure.Labile INR in prior users of warfarin.Concomitant use of: aspirin, antiplatelet or non-steroidal anti-inflammatory drug, lipid-lowering drug therapy, or CYP3A4 inhibitor.

This step will generate a group of ARISTOTLE-analogous apixaban patients, with similar baseline characteristics to ARISTOTLE subjects at the point of randomisation (n~9000).

The variables selected are expected to influence the likelihood of the outcomes of interest. Exact selection of matching variables will depend on the quality and completeness of the data available and a balance will be struck between matched sample size and balance. Different methods to facilitate selection of a matched cohort will be explored, such as propensity score matching (PSM) and coarsened exact matching (CEM),^13^ a non-parametric method that may give estimates with lower variance and bias for a given sample size compared than other methods.^14^

##### Step 3

The resulting trial matched sample of EHR apixaban patients will be matched to the warfarin ARISTOTLE-eligible EHR patients (figure 2) using a matching method such as PSM or CEM (final method selected based on giving optimal sample size vs balance). Risk set sampling will be employed in order to ensure similar duration of prior VKA/warfarin exposure for the prevalent users in the apixaban and warfarin EHR cohorts. The covariates for consideration in matching between EHR treatment arms or construction of a propensity score (PS) model will include the variables listed in step 2 along with additional EHR variables such as data source (Gold or Aurum), socioeconomic status and comorbidities. Each apixaban patient from the ARISTOTLE-eligible EHR patients will be matched 1:1 with the warfarin EHR patient with the closest match giving a trial-analogous cohort of ~18 000.

##### Step 4

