The absolute rates and HR for the outcomes of interest (time to: stroke/SE, MI, major bleeding and mortality) will then be calculated. For the primary outcome (time to stroke/SE) the EHR results will be validated against the ARISTOTLE trial results using the criteria detailed in the Statistical Analysis section (Validation of observational results against ARISTOTLE data).

#### Objective 2

We will select patient groups who would not have been included in ARISTOTLE (and therefore would not have been included in the Objective 1 cohort) or who are under-represented in ARISTOTLE. Specifically, this will include patient groups such as patients with an AF diagnosis in the EHR cohort meeting these additional criteria:

Severe comorbid condition: disease with a likelihood of causing death within 1 year or reasons making participation unpractical (such as dementia).

When matching the apixaban and warfarin patients within the patient groups for this objective, additional baseline variables will be considered compared with the list specified for Objective 1, Step 2; namely the H, A, and B components of the HAS-BLED score (Hypertension, Abnormal renal/liver function, Stroke, Bleeding history or predisposition, Labile INR, Elderly (>65 years), Drugs/alcohol concomitantly) not included for Objective 1 matching due to being ARISTOTLE exclusion criteria. In these special patient populations the same outcomes as Objective 1 will be assessed, with absolute and relative rates calculated separately in each special patient group.

#### Objective 3

We will select all patients with AF who have a prescription for apixaban, warfarin, rivaroxaban or dabigatran in the treatment period (between 1 January 2013 and 31 July 2019). The ARISTOTLE trial criteria will be applied, followed by matching the warfarin, rivaroxaban and dabigatran ARISTOTLE-eligible EHR patients in turn to the trial-eligible EHR apixaban patients following the methodology outlined in Objective 1, Step 3. This process will result in the creation of three trial-eligible EHR cohorts: warfarin users matched to apixaban users, rivaroxaban users matched to apixaban users and dabigatran users matched to apixaban users. Matched cohorts of excluded patient groups will also be constructed to enable pairwise comparisons of treatment effects in these groups using the method outlined in Objective 2. In all cohorts, the same outcomes as Objective 1 will be assessed with both absolute and relative treatment effects compared.

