#### Covariates

The variables to be considered for matching patients are detailed in the selection of participants for Objective 1 (Step 2).

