#### Limitations of the study design, data sources and analytical methods

Some of the criteria assessed for ARISTOTLE eligibility may not be well recorded in CPRD, criteria such as alcohol and drug abuse may not be captured for all patients. For criteria such as ‘increased bleeding risk’, it is unclear which codes to include and timescale to consider. These limitations are consistent with our aim to select a population as similar as possible to ARISTOTLE while acknowledging differences will remain. The most important risk factors for the primary outcome of stroke (the components of CHA2DS2-VASc score for AF stroke risk) are mostly well recorded in CPRD.^20^

There are differences in the coding systems used by the two EHR data sources and completeness of coding may differ between the two; the potential impact of this will be ascertained by comparisons of rates of diagnoses, baseline variables and prescriptions of interest. Inclusion of data source as a matching variable should prevent discrepancy between the sources from biasing results. We will explore different methods of combining Gold and Aurum, namely analysing separately by database and combining the results as a meta-analysis as an alternative to combining data before analysis.

The main focus of the study is validation of our methodology through assembling a cohort of patients comparable to the patients in ARISTOTLE and finding similar results to the trial. Criteria to determine the success of the methodology have been prespecified in the protocol. Given the use of CPRD data to determine treatment effectiveness is not yet well established, a finding that these data are not suitable to answer questions on intended effectiveness will be a useful conclusion.

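### Vascular disease and prior MI are named in no matching list, and the covariates stated for Objective 2 and the Objective 3 excluded groups leave them out, which mainly exposes the MI hazard ratio

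*Protocol article*

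**What the plan says.** Objective 1 has two matching steps with different purposes. Step 2 takes EHR apixaban patients to "create a cohort that matches the ARISTOTLE apixaban participants on a selection of the following baseline characteristics". Its 14 entries are age, sex, BMI, systolic blood pressure, the run "Congestive heart failure or left ventricular systolic dysfunction.Hypertension requiring treatment.Diabetes mellitus.Prior stroke/thromboembolism.Smoking status.Alcohol consumption.Level of renal impairment", prior VKA exposure, labile INR, and "Concomitant use of: aspirin, antiplatelet or non-steroidal anti-inflammatory drug, lipid-lowering drug therapy, or CYP3A4 inhibitor". The reason given for the choice is that "The variables selected are expected to influence the likelihood of the outcomes of interest".

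Step 3 matches warfarin patients to that apixaban group. It considers the Step 2 variables "along with additional EHR variables such as data source (Gold or Aurum), socioeconomic status and comorbidities". The comorbidities are not named.

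Three other places bear on the covariates:

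- **Covariates section:** "The variables to be considered for matching patients are detailed in the selection of participants for Objective 1 (Step 2"). Step 3 is not mentioned.
- **Objective 2:** the apixaban-warfarin match is described as the Step 2 list with additional variables, which are then identified as the H, A and B components of HAS-BLED.
- **Objective 3:** the trial-eligible cohorts follow Objective 1, Step 3. The excluded-group cohorts follow the Objective 2 method.

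Step 4 states that "The absolute rates and HR for the outcomes of interest (time to: stroke/SE, MI, major bleeding and mortality) will then be calculated", and Objectives 2 and 3 use the same outcomes. The limitations section says that "The most important risk factors for the primary outcome of stroke (the components of CHA2DS2-VASc score for AF stroke risk) are mostly well recorded" in CPRD.

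**The concern.** By the plan's own reasoning, matching variables are those expected to influence the outcomes, and the CHA2DS2-VASc components matter most for stroke. On the standard definition of that score, the Step 2 list supplies heart failure, hypertension, age, diabetes, prior stroke/thromboembolism and sex. It lacks vascular disease (prior MI, peripheral arterial disease, aortic plaque). No entry records coronary disease, although MI is an outcome and a previous MI is an obvious predictor of another.

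The match carries almost all the confounding control. Under Methods of analysis, the Cox model contains only treatment group and prior warfarin/VKA status. Applying the trial criteria does not balance vascular disease either, because it is not among the qualifying stroke risk factors in Step 1. If the match omits it and its prevalence differs between arms, the MI hazard ratio is biased, and those for stroke/SE and death may be too.

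A second consequence concerns transfer. Objectives 2 and 3 rest on methods validated in Objective 1. If the Objective 2 match uses a narrower covariate set than Step 3 did, it is not quite the method that was validated.

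**Working it through.** **1. Which text governs which comparison**

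| Match | Stated covariates | Vascular disease / prior MI |
|---|---|---|
| Obj 1 Step 2 (EHR apixaban to trial apixaban) | 14-entry list | Not named; no arm comparison is made here |
| Obj 1 Step 3 (apixaban v warfarin) | Step 2 list, data source, socioeconomic status, comorbidities | Not named; may be covered |
| Obj 2 (apixaban v warfarin) | Step 2 list plus HAS-BLED H, A, B | Not included |
| Obj 3, trial-eligible | As Step 3 | Not named; may be covered |
| Obj 3, excluded groups | As Obj 2 | Not included |
| Covariates section | Step 2 list | Not included |

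H, A and B are hypertension, abnormal renal/liver function, and bleeding history or predisposition. None of them records vascular disease.

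**2. Size of the possible bias**

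The plan has no figure of its own to reproduce here. For a binary confounder with the same risk ratio RR in both arms, and prevalence p1 on apixaban and p0 on warfarin:

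observed HR ≈ true HR × [1 + p1(RR − 1)] / [1 + p0(RR − 1)]

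RR, p1 and p0 are assumptions, because the documents give none of them.

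MI, RR 3:
- 15% v 20%: 1.30/1.40 = 0.929
- 20% v 15%: 1.40/1.30 = 1.077
- 10% v 20%: 1.20/1.40 = 0.857
- 20% v 10%: 1.40/1.20 = 1.167

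Stroke/SE, RR 1.5:
- 15% v 20%: 1.075/1.10 = 0.977
- 20% v 15%: 1.10/1.075 = 1.023
- 10% v 20%: 1.05/1.10 = 0.955
- 20% v 10%: 1.10/1.05 = 1.048

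Stroke/SE, RR 2, as a harsher case:
- 10% v 20%: 1.10/1.20 = 0.917
- 20% v 10%: 1.20/1.10 = 1.091

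**3. Could this change the validation result?**

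Validation applies to Objective 1 only and requires a stroke/SE HR between 0.69 and 0.99.

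- From the trial HR of 0.79, leaving the window needs a factor below 0.69/0.79 = 0.873 or above 0.99/0.79 = 1.253. Even the RR 2 case gives 0.79 × 0.917 = 0.72 to 0.79 × 1.091 = 0.86, which is inside.
- From the EU subgroup HR of 0.92, a factor above 0.99/0.92 = 1.076 is enough to leave. The RR 2 case with 20% v 10% gives 0.92 × 1.091 = 1.004, just outside. At RR 1.5 and the same prevalences, 0.92 × 1.048 = 0.96, inside.

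All of these are upper-end figures. They take a 5 or 10 point imbalance as surviving the match, whereas balance on antiplatelet and lipid-lowering drugs, and on any Step 3 comorbidities, would shrink it.

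**The case against.** A reader might infer that the Objective 1 hazard ratios are left confounded by vascular disease and that the validation is therefore unsound. The documents do not support this. Step 2 makes no apixaban-warfarin comparison, so an item missing there affects resemblance to the trial and cannot by itself bias a hazard ratio. Step 3 balances the arms, and prior MI or arterial disease falls within comorbidities in the ordinary sense. The list is open, and an article may leave the names to the full protocol. This part of the objection stands.

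The limitations section should not be over-read either. It says mostly well recorded, in a paragraph about capturing eligibility criteria, and does not promise that every component is a matching variable.

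The drug entries also count. Aspirin, antiplatelet and lipid-lowering drug use are correlates of vascular disease, and combined aspirin and thienopyridine treatment is an exclusion in Objective 1. They narrow the gap but do not close it: they record treatment, not the history of MI that predicts the outcome. The article also accepts that over-the-counter use of some concomitant drugs may be missed, although it expects this to be similar in both groups.

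Finally, the Figure 1 legend says the techniques validated in Objective 1 will be used in Objective 2, so the Step 3 additions may be meant to carry over. The Objective 2 text does not say so. It builds on Step 2, gives what reads as a closed set of additions, and omits Step 3, whereas Objective 3 cites Step 3 expressly for its trial-eligible cohorts. The general acknowledgement of residual confounding does not settle the matter, because vascular disease can be measured in these records.

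**Conclusion.** The point holds as a defect in the stated covariates for Objective 2, for the excluded-group cohorts of Objective 3, and in the Covariates section. Followed as written, those passages balance vascular disease and prior MI only through drug use and other correlates. For Objective 1 and the trial-eligible cohorts of Objective 3, confounding is not shown; the only weakness is that Step 3 does not name these items.

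The exposure is mainly the MI hazard ratio, a secondary outcome. Under the assumed inputs the MI bias factor is 0.93 (RR 3, 15% v 20%), or 0.86 to 1.17 (RR 3, 10% v 20% in either direction). For stroke/SE at RR 1.5 the shift is about 2% at 15% v 20% and 4 to 5% at 10% v 20%. That is unlikely to alter the validation result unless the true HR lies near 0.99. The direction of any imbalance is unknown. The change is worth making because it is cheap, but the point does not undermine the design.

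**What to change.** - Name vascular disease (prior MI, coronary or peripheral arterial disease) as a covariate in the arm-to-arm matches of Objective 1 Step 3, Objective 2 and Objective 3. Enter prior MI as a separate item because MI is an outcome.
- Add the same items to Step 2 if the trial baseline data allow. The documents do not show whether they do.
- Align the Covariates section with Step 3, and state in Objective 2 whether the Step 3 additions apply there.
- Report the balance of both items after each match, within the baseline tables already planned.

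The cost is one or two binary covariates from diagnosis codes in records already held. The downside is a slightly lower match rate under coarsened exact matching.

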**Figure 2 F2:**
[figure not shown]
Flow chart illustrating the assembly of a matched trial-analogous cohort of EHR patients. AF, atrial fibrillation; CPRD, Clinical Practice Research Datalink; EHR, electronic health record.

##### Step 1

We will select all (HES and ONS linked) patients in the EHR cohort (CPRD Gold and Aurum) who would have met the following *inclusion* criteria for the ARISTOTLE study, at least 6 months after patient registration in the database on or prior to the index date:

Diagnosis of AF.Age 18+ years.One or more stroke risk factors (age 75 years or older; prior stroke, transient ischaemic attack or SE; congestive heart failure; diabetes mellitus; hypertension).

In ARISTOTLE, patients randomised to apixaban were new users of apixaban while both treatment arms were allowed to be previous users of warfarin, with patients stratified by prior warfarin/VKA exposure. To mirror ARISTOTLE, we will assess trial criteria for apixaban patients on the date of their first prescription of apixaban while allowing patients prescribed warfarin to become eligible at any warfarin prescription date during the study period; furthermore, we will match ARISTOTLE in the proportion of new versus prevalent users in both treatment arms. We will then exclude patients who meet any of the following ARISTOTLE study *exclusion* criteria prior to their eligible-for-inclusion date:

AF due to reversible causes.Mitral stenosis.Increased bleeding risk.Conditions other than AF requiring chronic anticoagulation.Persistent, uncontrolled hypertension.Active infective endocarditis.Current treatment with aspirin >165 mg/day.Simultaneous current treatment with both aspirin and a thienopyridine.Conditions likely to interfere with participation in the trial or cause death within 1 year.Recent alcohol or drug abuse, or psychosocial reasons making study participation impractical.Recent ischaemic stroke (within 7 days).Severe renal insufficiency.Alanine aminotransferase or aspartate aminotransferase >2× upper limit of normal (ULN) or total bilirubin ≥1.5× ULN.Platelet count ≤100 x10^9^/LHaemoglobin <90 g/L.Pregnancy or breast feeding.

Feasibility counts in Gold found approximately 60% of patients with AF prescribed apixaban met the ARISTOTLE trial criteria. Details of the algorithms used in applying the trial criteria to the EHR data are given in the online supplemental file.

10.1136/bmjopen-2020-042947.supp1Supplementary data

##### Step 2

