### Statistical analysis

#### Methods of analysis

ARISTOTLE used an intent-to-treat (ITT) approach for the primary efficacy analysis and an on-treatment approach for sensitivity analysis and safety outcomes. We will perform equivalent analyses by using two different censoring schemes: a primary censoring scheme censoring 5 years after index date (reflecting the maximum possible follow-up in ARISTOTLE) for the primary effectiveness analyses, and an on-treatment scheme censoring around time of last study drug for the sensitivity analysis and safety outcome. For the on-treatment censoring scheme, date of last exposure will be estimated using patient prescription data—to allow for drug half life, stockpiling of tablets and less than 100% adherence we will add 30 days after the apparent end of treatment.

Demographic and baseline variables will be presented before and after matching steps. As the primary analysis accounts neither for treatment switching nor discontinuation, the proportion of patients discontinuing treatment and time to treatment discontinuation will be tabulated.

The primary effectiveness endpoint is time to first occurrence of confirmed stroke (ischaemic, haemorrhagic or unspecified type) or SE during the study, regardless of whether the subject is receiving treatment at the time (primary censoring scheme). Comparisons will be made according to prescribed treatment (apixaban vs warfarin).

All time to event endpoints will be analysed using a Cox proportional hazards model including treatment group as a covariate and prior warfarin/VKA status (experienced, naïve). Point estimates and two-sided 95% CIs will be constructed for the outcome. Absolute event rates of all outcomes of interest will also be calculated.

Secondary outcomes cover the key safety outcome of major bleeding and the individual outcomes of stroke, SE, MI and mortality. Secondary outcomes other than major bleeding will use the ITT censoring scheme, major bleeding will use the on-treatment censoring scheme.

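### Step 3 aligns VKA-experienced patients on how long they took warfarin, not on how recent any prior event was, so the experienced-stratum hazard ratio may be biased and the pooled model would not show it

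*Protocol article*

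**What the plan says.** All references are to the protocol article.

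- **Index dates** (Selection of participants, Objective 1, Step 1). For apixaban, "we will assess trial criteria for apixaban patients on the date of their first prescription of apixaban". For warfarin, the design differs by "allowing patients prescribed warfarin to become eligible at any warfarin prescription date during the study period". The stated reason is to mirror the trial: "In ARISTOTLE, patients randomised to apixaban were new users of apixaban while both treatment arms were allowed to be previous users of warfarin".
- **Alignment of prevalent users** (Step 3). "Risk set sampling will be employed in order to ensure similar duration of prior VKA/warfarin exposure for the prevalent users" in the two EHR arms.
- **Matching variables** (Step 2, carried into Step 3). The list contains "Prior stroke/thromboembolism" with no timing attached, prior VKA exposure, and "Labile INR in prior users of warfarin". Step 3 adds an open set that includes data source, socioeconomic status and comorbidities. All are for consideration, not final.
- **Recency and bleeding** (Step 1 exclusions). The only stated rule on how recent a stroke may be is the 7-day exclusion for ischaemic stroke. Increased bleeding risk is an exclusion. The limitations section says its codes and time window are not settled.
- **Model** (Methods of analysis). A Cox model with treatment and prior VKA status, experienced or naïve. No interaction or stratum-specific HR is stated.
- **Assurance** (Plan for addressing confounding). Eligibility criteria plus baseline matching are expected to prevent channelling bias in Objective 1. Residual confounding is acknowledged in general terms.
- **Validation rule**. The stroke/SE HR must lie between 0.69 and 0.99.

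**The concern.** In ARISTOTLE, randomisation decided whether a warfarin-experienced patient moved to apixaban or stayed on warfarin. In the EHR cohort a prescriber decides. A VKA-experienced apixaban patient is often indexed at the moment of that decision, while the warfarin comparator can be indexed at a routine repeat prescription where nothing has happened. Matching on duration of warfarin use makes the two alike in length of exposure but says nothing about what preceded the index date.

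One reason for leaving warfarin, labile INR, is handled. Recency of a stroke is not named. As listed, a patient switched a few weeks after a stroke could be paired with a stable warfarin patient whose stroke was years earlier, since both have the listed history and both clear the 7-day rule. Any excess early risk after the recent stroke would then be counted in apixaban follow-up.

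At stake is how the validation result is read. The range reaches up to 0.99 because the authors anticipate a weaker effect in routine care. Bias against apixaban in one stratum would look the same as that attenuation, and a single pooled HR cannot separate the two.

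**Working it through.** **The plan's own figures.** The article gives no number for this point. Its one computed figure reproduces: 23 526 × 0.60 = 14 115.6 (stated 14 115), and 8400 + 14 115 = 22 515 (stated >22 000). It has no bearing on the bias.

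**Room before the upper limit.** From the trial's 0.79, a bias factor of 0.99/0.79 = 1.253 is needed to reach 0.99. From the EU-subgroup figure of 0.92, 0.99/0.92 = 1.076 is enough.

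**Size, first calculation.** All inputs are assumptions. Among matched VKA-experienced patients with prior stroke, 25% of switchers and 3% of stayers had a recent stroke, and recency triples the hazard.

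- Factor in that subset: (1 + 0.25×2)/(1 + 0.03×2) = 1.50/1.06 = 1.415.
- If the subset supplies 15% to 30% of events, the pooled factor is 1 + 0.15×0.415 = 1.062 to 1 + 0.30×0.415 = 1.125.
- A true 0.79 becomes 0.84 to 0.89. A true 0.92 becomes 0.98 to 1.03.
- Milder inputs (10% against 2%, hazard doubled): 1.10/1.02 = 1.078, pooled 1.012 to 1.024.

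**Size, second calculation.** Prior stroke is held balanced between arms and only recency differs. Within the experienced stratum

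B = [1 − q + q·h·(1 + r1(RR − 1))] / [1 − q + q·h·(1 + r0(RR − 1))],

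and the pooled factor is B^s. Assumed: prior-stroke share q = 0.20; HR for prior stroke h = 2.5; experienced share s = 0.4 to 0.6. Here r1 and r0 are the recent shares among prior strokes in the apixaban and warfarin arms. RR is the recent-versus-remote hazard ratio averaged over follow-up, taken as 1.5 to 3.

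| r1 / r0 | B | pooled factor | 0.79 becomes | 0.92 becomes |
|---|---|---|---|---|
| 0.10 / 0.02 | 1.02–1.06 | 1.01–1.04 | 0.80–0.82 | 0.93–0.95 |
| 0.30 / 0.02 | 1.05–1.21 | 1.02–1.12 | 0.81–0.89 | 0.94–1.03 |
| 0.50 / 0.05 | 1.09–1.33 | 1.03–1.19 | 0.82–0.94 | 0.95–1.09 |

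Example (0.30 / 0.02, RR = 3): B = (0.80 + 0.50×1.60)/(0.80 + 0.50×1.04) = 1.60/1.32 = 1.212. With s = 0.6 the pooled factor is 1.212^0.6 = 1.122, so 0.92 becomes 1.03.

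No scenario takes 0.79 to 0.99. Several take 0.92 past it, all with recent events much commoner among switchers and a large excess hazard. The upper RR values are generous if the excess risk is early, because follow-up runs to 5 years and RR is an average over it.

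**Would the stated analyses show it?** The sensitivity analyses cover on-treatment censoring, switching after index, adherence, INR control, early adopters, derived index dates and prescription gaps. None is stated to separate naïve from experienced pairs. The earlier-index-date analysis is described for new initiators. A main effect for VKA status lets baseline hazard differ by stratum but still forces one treatment effect.

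**The case against.** The strongest reply is that this is a condensed article. The covariate list is open and provisional, coding is not given, and the full protocol or analysis plan could add recency and stratum HRs. That stands against any claim that recency will certainly be ignored. A reader might infer that prior stroke is matched only as yes or no; the text gives no coding, so that is inference. It does not rescue the text as written, which names duration as what risk set sampling is meant to equalise and then expects channelling bias to be avoided.

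Other objections stand and limit the point:

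- A reader might infer that bleeds on warfarin enter as ever/never history. They do not. Bleeding risk is an exclusion in Objective 1, and the Objective 2 text says this is why the corresponding HAS-BLED components are left out of Objective 1 matching.
- A reader might infer that every VKA-experienced apixaban patient switched at index because of an event. Previous users may have stopped earlier, and no reasons for switching are reported. The direction of bias is therefore likely rather than established.
- A reader might conclude that validation should also require the VKA-naïve HR to lie in the range. The range was set against ARISTOTLE's HR of 0.79 in a mixed population, and the naïve HR would be less precise. That trade-off is debatable and does not follow from the documents.
- Objective 3 reuses Step 3, but two of its three comparisons set one DOAC against another, so the switch-versus-stay contrast does not simply carry over.

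The general acknowledgement of unmeasured confounding does not answer the point, since event timing should be derivable from the linked hospital and primary care data.

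**Conclusion.** The point holds as a possible bias that the stated design does not address. For VKA-experienced pairs the index dates differ in kind, risk set sampling is specified for duration only, and prior stroke carries no timing beyond the 7-day exclusion. The expectation that matching removes channelling bias is too strong for this stratum.

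The size is unknown. On assumed inputs the pooled stroke/SE HR shifts by about 1% to 12%, reaching 19% only where every input sits at its extreme. A true 0.79 stays inside 0.69 to 0.99 throughout. The validation decision is exposed only if the true EHR effect is near the upper limit, for example the EU figure of 0.92. A reader might infer a demonstrated bias, or that validation is bound to fail or mislead; the documents support neither. This is a worthwhile, inexpensive improvement.

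**What to change.** 1. In Step 3, for the VKA-experienced risk sets, add time since last stroke/TIA/SE and recent hospital admission (including for bleeding, where not already excluded) to the matching or propensity score covariates, all measured at the risk-set date.
2. Report the stroke/SE HR separately for VKA-naïve and VKA-experienced pairs, with a treatment-by-prior-VKA interaction, as a supporting analysis for the validation conclusion. Leave the validation rule on the pooled HR.
3. Reword the plan for addressing confounding to say that eligibility criteria and matching are intended to reduce channelling bias, and that prescriber-chosen switching in VKA-experienced patients remains a specific concern.

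Cost: covariate derivation from linked data already in the study, and two extra HRs. Some recently hospitalised switchers may go unmatched, which reduces the sample and narrows the population slightly. The stratum confidence intervals will be wider than the pooled one, so a non-significant interaction should not be read as proof that the strata agree.

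### Step 3 aligns prior warfarin use by duration but not by recency, so lapsed users starting apixaban can be paired with continuing warfarin users

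*Protocol article*

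**What the plan says.** The protocol article sets the two entry rules in Selection of participants, Objective 1, Step 1. For one arm, "we will assess trial criteria for apixaban patients on the date of their first prescription of apixaban". The other arm is built by "allowing patients prescribed warfarin to become eligible at any warfarin prescription date during the study period". The same paragraph adds that "we will match ARISTOTLE in the proportion of new versus prevalent users in both treatment arms".

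VKA history is then handled in three places:

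- **Matching variables (Step 2).** The list contains "Prior VKA/warfarin exposure.Labile INR in prior users of warfarin". Step 3 carries these into the between-arm match: the candidate covariates "will include the variables listed in step 2 along with additional EHR variables such as data source (Gold or Aurum), socioeconomic status and comorbidities".
- **Risk sets (Step 3).** "Risk set sampling will be employed in order to ensure similar duration of prior VKA/warfarin exposure for the prevalent users in the apixaban and warfarin" arms.
- **Model (Methods of analysis).** The Cox model has a two-level term for prior VKA status, experienced or naïve.

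The article does not define a prevalent user. It states no maximum gap since the last VKA prescription and does not require an experienced apixaban patient to have switched directly from warfarin.

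**The concern.** The entry rules treat the arms differently. A warfarin patient enters on a day with a warfarin prescription, so at index that patient is starting, continuing or restarting the drug. An apixaban patient enters at the first apixaban prescription and may have stopped warfarin the week before or years before.

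Take an apixaban starter who used warfarin for two years and stopped three years ago, and a comparator with two years of unbroken use. They agree on prior exposure and on its duration, and the model puts both in the experienced group. They differ in current protection, in whether they stayed on warfarin, and perhaps in why one of them left it. In ARISTOTLE, randomisation stratified by prior VKA exposure would balance recency between arms in expectation. Here the entry rules can create an imbalance that the stated balancing does not address.

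The HR affected is the one tested in Validation of observational results against ARISTOTLE data, and Objectives 2 and 3 go ahead only if that test succeeds. The planned sensitivity analyses cover discontinuation after index, early adopters, and derived index and last-dose dates. None looks at the recency of earlier warfarin use.

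**Working it through.** **1. What each device separates**

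| Device | Separates a lapsed from a current user with equal prior duration? |
|---|---|
| Prior VKA exposure (Step 2) | No |
| Labile INR in prior users (Step 2) | Not directly; it describes INR control |
| Duration of prior exposure (Step 3 risk sets) | No |
| Experienced/naïve term (Cox model) | No |

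**2. Plan figures used**

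- Feasibility (Sample size): 23 526 × 0.60 = 14 115.6, stated as 14 115. Then 8400 + 14 115 = 22 515, stated as >22 000. Both reproduce.
- Precision: the ARISTOTLE interval 0.66 to 0.95 gives SE = ln(0.95/0.66)/(2 × 1.96) = 0.0929. Using this for the EHR cohort of about 18 000 is an assumption; the article gives no expected event count.
- Validation: HR between 0.69 and 0.99, and upper 95% limit below 1.52. At HR 0.99 the upper limit is 0.99 × exp(1.96 × 0.0929) = 1.19, so the second criterion does not bind at this precision.

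**3. Starting from 0.79**

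Let q be the share of the whole apixaban arm that is lapsed and paired with current users, and let 1.3 be the confounding rate ratio in those pairs. Both are assumed. Then:

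- ln HR = ln 0.79 + q ln 1.3
- P(superiority) = Φ(−ln HR/0.0929 − 1.96)
- P(validation) = Φ[(ln 0.99 − ln HR)/0.0929] − Φ[(ln 0.69 − ln HR)/0.0929]

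| q | HR | P(superiority) | P(validation) |
|---|---|---|---|
| 0 | 0.79 | 72% | 92% |
| 0.1 | 0.81 | 62% | 94% |
| 0.2 | 0.83 | 50% | 95% |
| 0.3 | 0.85 | 39% | 93% |

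The validation chance does not fall because, with no bias, most of the failures lie below 0.69. A modest upward bias moves the estimate towards the middle of the window.

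**4. Starting from 0.92**

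The plan expects that the effect may be weaker than in the trial and cites 0.92 for EU patients. Let p be the VKA-experienced share (event-weighted), f the share of experienced apixaban patients who are lapsed and paired with current users, and r the stroke/SE rate ratio of lapsed to persistent users. All three are assumed.

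- Bias factor = (1 + f(r − 1))^p
- p = 0.5, f = 0.3, r = 1.5: 1.15^0.5 = 1.07, so 0.92 becomes 0.987 and 0.79 becomes 0.85.
- P(estimate > 0.99) from 0.92: 1 − Φ[(ln 0.99 − ln 0.92)/0.0929] = 1 − Φ(0.79) = 21%.
- From 0.987: 1 − Φ(0.04) = 49%.

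**5. Range**

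Over p = 0.4-0.6, f = 0.05-0.5 and r = 0.8-2.0, the factor runs from 0.94 to 1.28. For f at or below 0.1 it stays within 0.99-1.06. Reaching 0.99 needs a factor of 0.99/0.79 = 1.25 from 0.79, but only 0.99/0.92 = 1.08 from 0.92. From 0.79, only the most extreme corner tested (p = 0.6, f = 0.5, r = 2.0) leaves the window, at 1.008.

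**The case against.** The strongest reply is that prevalent users can be read as current users, which would make the experienced apixaban patients direct switchers, and that a gap rule is the kind of detail a condensed article leaves to the full protocol. Part of this stands: the term is undefined and the full protocol is not shown. But Step 1 moves between previous and prevalent users without distinguishing them. The supplement is cited there only for the algorithms that apply the trial criteria. The article does state the balancing target, and it is duration. If prevalent does mean current, a lapsed apixaban starter falls outside the risk-set rule, yet by history still counts as experienced in the model and has no stated comparator rule.

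A reader might infer four stronger things that the documents do not support:

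- **Duration is all that is balanced.** Prior exposure, labile INR, prior stroke, renal impairment, concomitant drugs and comorbidities are also candidates, and the bleeding-risk exclusion may remove some patients who stopped after a bleed. These may absorb part of the difference, although the limitations section says the codes and timescale for that exclusion are unclear.
- **Every experienced comparator is a persistent user.** Entry at any warfarin prescription date also admits restarters.
- **The HR in lapsed pairs is 1.3 outright.** That gives cohort HRs of 0.87-0.92 and superiority of 31-15% at shares of 20-30%, but it implies confounding of 1.3/0.79 = 1.65. If 1.3 is the confounding, lapsed pairs have HR 0.79 × 1.3 = 1.03, and the table above applies.
- **A sound method would fail validation.** Validation does not require superiority. From a true 0.79, the chance of passing is not materially reduced over the range in that table.

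**Conclusion.** The gap is in the text: entry is asymmetric with respect to current warfarin use, and nothing stated captures time since the last VKA prescription. The result can be a biased Objective 1 HR; the documents do not show that it will be. The direction is probably against apixaban, because lapsed users may have stopped after problems and comparators lean towards patients who stayed on the drug. Other reasons for stopping could push it the other way.

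The size is unknown. It rests on an assumed lapsed share, an assumed relative risk and precision borrowed from ARISTOTLE. If few patients are lapsed it is negligible. If the true HR is near 0.79, the main loss is in the chance of concluding superiority, not of validation. If it is near 0.92, a factor of 1.07 takes the estimate to the edge of the window and makes exceeding 0.99 close to an even chance. The change is cheap and worth making, but this is not evidence that the planned validation is unsound.

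**What to change.** In Step 3:

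1. Define a prevalent user by time since the last VKA prescription at index, with the maximum gap stated.
2. Form the risk sets, or match, on both duration of prior VKA use and time since the last VKA prescription. Direct switchers are then paired with continuing users, and lapsed apixaban starters with patients restarting warfarin after a similar gap.
3. Where no such restarter exists, leave the lapsed apixaban patient unmatched and report how many there are.
4. Tabulate time since last VKA by arm with the other baseline variables.
5. Add a sensitivity analysis limited to naïve patients plus direct switchers versus continuing users.

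The cost is one more variable, taken from prescribing records that the study already uses. The downside is that some of the roughly 9000 apixaban patients selected in Step 2 may go unmatched, which could disturb the similarity to ARISTOTLE. That balance should be rechecked after Step 3. The pool of more than 22 000 eligible apixaban patients leaves room to replace them.
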